### **7.0 SAFETY (Reference: Protocol p. 19)**

We do not anticipate any adverse events as a result of this study. The greatest risk is potential breach of confidentiality regarding sensitive information (e.g., use of drugs and alcohol). To protect against this possibility, we will use randomly generated study identifiers, created by a computer, in all surveys, transcripts and databases. Code keys that link the study identifier to the subject identity (medical record number, name, and telephone number) will be maintained throughout the study period. The keys will be stored and locked (password-protected) in a secure location.

Although not induced by study participation, serious substance use may be detected during completion of the assessment batteries. We will follow the same guidelines for assessment of risk related to substance use that has been used in protocols previously approved by the BCH institutional review board. If a participant responds “yes” to consuming 10 or more alcoholic drinks in one occasion within the past 3 months, using sedatives (such as benzodiazepine, opioids, barbiturates, or pain medication) in combination with alcohol, using stimulants (such as Adderall or Ritalin) in combination with alcohol, or using illegal drugs other than marijuana (such as cocaine, or Ecstasy) monthly, the RA will notify the primary clinician.

At baseline, the RA will locate the primary clinician in the clinic following completion of the assessment battery. The primary clinician will be able to re-interview the patient, as clinically warranted, and determine what further action should be taken. The RA will also notify the primary clinician if there is any indication or concerns about the participant’s risk for imminent harm. We will ask the primary clinician to sign our Alcohol Safety Sheet (see attached) to indicate that he/she has been notified. We will tell participants that we cannot make absolute assurances or provide them with specific guidelines on parental notification.

We will explain that we will only inform their clinician and that the clinician will decide if a participant’s parents should be notified based on the best clinical judgment at the time. We will assure participants that we will make every effort *to inform them before the fact* when breach of confidentiality is required, to include them in a discussion regarding the exact details that are to be released and to release as few details as possible to ensure the safety of the adolescent (or other person).

Although not induced by study participation, depressive symptoms may also be detected during the baseline study assessment through completion of the PHQ-2. If a participant scores 3 or greater on the PHQ-2, indicating a non-acute need for further assessment, the RA will inform the participant that we will be notifying his/her provider, who may follow up with them by phone, or at their next appointment. We will notify the participant's provider of the PHQ-2 score via secure e-mail by the end of the day. We will ask that the provider reply to our e-mail to confirm that he or she has been notified of the safety concern. The provider will then address the mental health safety concern according to standard clinical practice. If the RA does not receive confirmation of receipt from the clinician, the RA will follow up with a phone call and/or page to ensure that the message is received. Both Principal Investigators ([name] and [name]) will be alerted of all safety concerns via email.

At 6 and 12 months follow up safety concerns may also arise through completion of the assessment batteries. We will address follow up safety flags through secure e-mails to the participant's specialty care clinician. We will notify the clinician via secure e-mail if a participant has a PHQ-2 score of 3 or higher (indicating a non-acute need for further assessment), or if serious substance use is detected (high volume alcohol consumption or use of sedatives in combination), and request confirmation that the participant's clinician has received the notification and is using standard clinical protocol to determine appropriate follow-up and/or referrals. If we do not receive confirmation of receipt from the clinician, we will follow up with a phone call and/or page to ensure that the message is received. We will provide email notification to clinicians of any safety flags raised within 48 hours of survey completion.

We will provide participants with contact information for their primary and specialty care providers if they wish to talk to a health professional or obtain help regarding substance use and/or mental health. A text message or email will also be sent to participants via BCH's outlook email system with the names and telephone numbers of two resources outside of BCH they may call if they wish to talk to a professional or gain help regarding substance use and/or mental health. If the participant does not readily know their cell phone carrier, which is required for sending the text message via email, an external website will be utilized to identify the cell phone carrier. Participant will also be provided verbally with the contact numbers for these resources upon request, or if they do not wish to receive a text message, but would still like the information.

It is also possible, but unlikely, that some participants could become upset by items in the measurement battery or information presented in the intervention or control arms. We include statements at the start that participants may skip questions that they are uncomfortable answering, that they may stop the study at any time, and that they may speak with the RA after completing the measurement if they have any questions or concerns about the questions asked or the material presented.

Given the nature of the study, we anticipate few if any adverse events. If we determine during the course of the study that an adolescent or someone else is at serious risk of harm, we will notify their provider. We will inform adolescents of this before we ask them to assent to participation in the study. We do not anticipate any serious adverse events, such as medical complications or deaths, as a result of this project.

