467 we will ask all participants about prescription drug use regardless of their use of other substances.  
468 Following the format of the S2BI, questions about other psychoactive substances including illegal  
469 drugs (such as cocaine or Ecstasy), inhalants (such as nitrous oxide), and herbs and synthetic drugs  
470 (such as salvia, "K2" or bath salts) will be asked only if participants answer yes to either alcohol,  
471 marijuana, or tobacco use.

472 **Criterion standard for substance use disorder diagnosis:** If participants answer no to past 12  
473 month alcohol, marijuana, or tobacco use they will be asked a question about lifetime use of these  
474 substances. Questions about lifetime use were taken from the Computerized Diagnostic Interview  
475 Schedule for Children – 4 (DISC-IV).

476 **Alcohol safety screen:** We will include questions about frequency and severity of alcohol use that  
477 will be used as safety flags. If a patient reports consuming 10 or more drinks containing alcohol in the  
478 past three months, or using sedatives in combination with alcohol, the RA will notify the primary  
479 clinician (See Adverse Event Criteria and Reporting Procedures)

480 **Prescription medication misuse:** Abuse of prescription medications among youth has risen  
481 dramatically in recent years. We will ask questions to assess if participants take medication as  
482 prescribed by their doctor. We will also assess medication diversion, with a specific interest in patients  
483 who are being prescribed stimulant medications. These questions were adapted from previous  
484 studies on prescription medication misuse among adolescents.

485 **Criterion standard substance use frequency measure:** Each participant who reports any alcohol  
486 use will complete a 90-day Timeline Follow Back (TLFB) calendar that records frequency and quantity  
487 of alcohol use and frequency of marijuana use. The 90-day TLFB has been demonstrated to be both  
488 valid and reliable in adolescents. Participants will complete the TLFB on the computerized tablet  
489 following completion of the assessment battery. The TLFB is self-administered; participants will view  
490 an electronic calendar of the past 90 days and will input if they used marijuana on a given day and/or  
491 number of drinks consumed on a given day. If participants have not used marijuana or consumed a  

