## 656 E. Adverse Event Criteria and Reporting Procedures

657 We do not anticipate any adverse events as a result of this study. The greatest risk is potential  
658 breach of confidentiality regarding sensitive information (e.g., use of drugs and alcohol). To protect  
659 against this possibility, we will use randomly generated study identifiers, created by a computer, in all  
660 surveys, transcripts and databases. Code keys that link the study identifier to the subject identity  
661 (medical record number, name, and telephone number) will be maintained throughout the study  
662 period. The keys will be stored and locked (password-protected) in a secure location.

663 Although not induced by study participation, serious substance use may be detected during  
664 completion of the assessment batteries. We will follow the same guidelines for assessment of risk  
665 related to substance use that has been used in protocols previously approved by the BCH  
666 institutional review board. If a participant responds “yes” to consuming 10 or more alcoholic drinks  
667 in one occasion within the past 3 months, using sedatives (such as benzodiazepine, opioids,  
668 barbiturates, or pain medication) in combination with alcohol, using stimulants (such as Adderall or  
669 Ritalin) in combination with alcohol, or using illegal drugs other than marijuana (such as cocaine, or  
670 Ecstasy) monthly, the RA will notify the primary clinician. At baseline, the RA will locate the primary  
671 clinician in the clinic following completion of the assessment battery. The primary clinician will be  
672 able to re-interview the patient, as clinically warranted, and determine what further action should  
673 be taken. The RA will also notify the primary clinician if there is any indication or concerns about  
674 the participant’s risk for imminent harm. We will ask the primary clinician to sign our Alcohol Safety  
675 Sheet (see attached) to indicate that he/she has been notified. We will tell participants that we  
676 cannot make absolute assurances or provide them with specific guidelines on parental notification.  
677 We will explain that we will only inform their clinician and that the clinician will decide if a  
678 participant’s parents should be notified based on the best clinical judgment at the time. We will  
679 assure participants that we will make every effort *to inform them before the fact* when breach of  

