**Substance use screen:** We will administer the Screening to Brief Intervention (S2BI) to ask about alcohol, tobacco, marijuana, prescription drug, and other substance use over the past 12 months. S2BI was developed at BCH with support from NIDA. In the original S2BI, questions on prescription drug use are asked only if patients answer yes to using alcohol, marijuana, or tobacco. In this study we will ask all participants about prescription drug use regardless of their use of other substances. Following the format of the S2BI, questions about other psychoactive substances including illegal drugs (such as cocaine or Ecstasy), inhalants (such as nitrous oxide), and herbs and synthetic drugs (such as salvia, “K2” or bath salts) will be asked only if participants answer yes to either alcohol, marijuana, or tobacco use.

**Criterion standard for substance use disorder diagnosis:** If participants answer no to past 12 month alcohol, marijuana, or tobacco use they will be asked a question about lifetime use of these substances. Questions about lifetime use were taken from the Computerized Diagnostic Interview Schedule for Children – 4 (DISC-IV).

**Alcohol safety screen:** We will include questions about frequency and severity of alcohol use that will be used as safety flags. If a patient reports consuming 10 or more drinks containing alcohol in the past three months, or using sedatives in combination with alcohol, the RA will notify the primary clinician (See Adverse Event Criteria and Reporting Procedures)

**Prescription medication misuse:** Abuse of prescription medications among youth has risen dramatically in recent years. We will ask questions to assess if participants take medication as prescribed by their doctor. We will also assess medication diversion, with a specific interest in patients who are being prescribed stimulant medications. These questions were adapted from previous studies on prescription medication misuse among adolescents.

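### The alcohol level that triggers clinician notification is stated two ways: ten or more drinks on one occasion, and ten or more drinks over three months

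*Supplement*

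**What the plan says.** SAP 7.0 (Safety) sets out when serious substance use found in the assessment batteries is passed to the primary clinician. It lists four triggers:

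- a yes answer "to consuming 10 or more alcoholic drinks in one occasion within the past 3 months";
- sedatives combined with alcohol;
- stimulants taken along with alcohol;
- "or using illegal drugs other than marijuana (such as cocaine, or Ecstasy) monthly, the RA will notify the primary clinician".

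Protocol E (Adverse Event Criteria and Reporting Procedures) carries the same list, including the single-occasion condition: "in one occasion within the past 3 months, using sedatives (such as benzodiazepine, opioids".

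The alcohol safety screen in SAP 2.2.5 states the rule more briefly: "If a patient reports consuming 10 or more drinks containing alcohol in the past three months", or sedatives with alcohol. Protocol D has the same sentence: "past three months, or using sedatives in combination with alcohol, the RA will notify the primary". In both documents this sentence ends with a pointer to the adverse event section.

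For 6 and 12 months, SAP 7.0 and Protocol E have the clinician notified by e-mail if the PHQ-2 score is 3 or higher, or "if serious substance use is detected (high volume alcohol consumption or use of sedatives in combination".

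**The concern.** The same action, notification of the primary clinician, is attached to two alcohol levels that are far apart. One describes an extreme single episode. The other, taken at its word, is a cumulative total that an occasional drinker reaches.

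The level decides whose drinking is disclosed. SAP 7.0 states: "The greatest risk is potential breach of confidentiality regarding sensitive information". Once notified, the clinician may re-interview the adolescent and decides whether parents are told. Staff explain before assent that a provider may be informed, so they need a single rule to describe. The May 2017 amendment allows other study sites, which makes it more useful that the written rule can be read only one way.

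**Working it through.** This is mainly a comparison of text. The plan gives no figure to reproduce.

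**Step 1. The statements side by side.**

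| Place | Alcohol level | Other triggers |
|---|---|---|
| SAP 7.0; Protocol E | at least 10 drinks on one occasion, past 3 months | sedatives with alcohol; stimulants with alcohol; monthly illegal drugs other than marijuana |
| SAP 2.2.5; Protocol D | at least 10 drinks, past three months, no occasion stated | sedatives with alcohol |
| SAP 7.0 and Protocol E, 6 and 12 months | high volume, in a parenthesis | sedatives in combination |

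**Step 2. What the screen wording means as a total.** I take three months as 90 days, the window of the Timeline Follow Back calendar.

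- 90 / 7 = 12.9 weeks.
- 10 drinks / 12.9 weeks = 0.78, or about 0.8 drinks per week.

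**Step 3. Cases on which the rules disagree.**

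- One drink on each of 10 days: total 10, largest occasion 1. Reported under SAP 2.2.5 and Protocol D, not under SAP 7.0 and Protocol E.
- One drink a week: total about 13, largest occasion 1. Same disagreement.
- Ten drinks at one party: total at least 10, largest occasion 10. Reported under both.

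The disagreement runs one way. Whoever meets the single-occasion rule also meets the total rule, but not the reverse.

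**Step 4. Is it settled elsewhere?** The amendment summary does not mention the notification level, and none of the dated updates in SAP section 11 touches it. Both wordings stand together in the SAP and in the protocol, so this is not a difference between versions.

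**Step 5. The follow-up text.** SAP 7.0 introduces serious substance use as something detected in the assessment batteries, in the plural, and gives the numeric criteria there. Its separate instruction for baseline comes afterwards. The follow-up paragraph uses the same term again, so the numeric level can be carried forward. Its parenthesis, however, names only alcohol volume and sedatives. Stimulants with alcohol and monthly illegal drug use are missing.

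**The case against.** The strongest reply is that the documents already show which text governs. The screen sentence is a short description of a measure and sends the reader to the adverse event section, which holds the full trigger list, the research assistant's steps, the sign-off sheet and the timing. The screen sentence is plainly abbreviated, since it also omits two other triggers. A dropped phrase is the natural explanation. This largely stands: the single-occasion rule is probably intended. But neither document states precedence, and the screen sentence reads as a complete rule by itself.

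A second reply is that the questionnaire item sets the level in practice, because SAP 7.0 refers to a yes answer. The battery and the Alcohol Safety Sheet are attachments not shown here, and the batteries were revised in 2017. This also stands. Whether any research assistant faced a real ambiguity cannot be shown, though the written sentences would still disagree.

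Three stronger readings are tempting and are not supported:

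- **That follow-up has no alcohol threshold.** The repeated term can be read back to the numeric criteria, as Step 5 shows. The parenthesis is an incomplete paraphrase.
- **That the number of adolescents wrongly reported can be estimated.** Protocol C gives past-year alcohol use of 30.8% overall and 36.5% in high school youth in a prior study. If those rates applied to 450 participants, the total rule could reach at most 450 × 0.308 = 139 to 450 × 0.365 = 164. That is a ceiling, not a count. Subtracting the binge-drinking rate does not isolate those whom only the total rule reports: someone who has five drinks on three occasions totals 15 but never reaches 10 on one occasion. Protocol C gives neither three-month totals nor a binge definition.
- **That the discrepancy biases the treatment comparison.** The rule is the same in both arms and enters no outcome definition.

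**Conclusion.** The point holds as a minor inconsistency. The notification level is wrong in one of the two places where each document states it, and the likely error is the missing single-occasion condition in SAP 2.2.5 and Protocol D. Taken literally, that text puts the level at about 0.8 drinks per week and would disclose light drinking that the adverse event section does not. The follow-up parenthesis is incomplete by two triggers.

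The conclusion rests on the wording and needs no assumption beyond reading three months as 90 days for the weekly figure. That the single-occasion rule is intended is an inference from the cross-reference. Sample size, power and significance level are untouched, and no effect on the trial estimate is claimed.

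**What to change.** - In the alcohol safety screen sentence of SAP 2.2.5 and Protocol D, insert the words *in one occasion* so that it matches SAP 7.0 and Protocol E. If the total was in fact intended, change SAP 7.0 and Protocol E instead.
- In the 6- and 12-month paragraph of SAP 7.0 and Protocol E, replace the parenthesis with a reference to the full criteria given earlier in the same section. If stimulants with alcohol and monthly illegal drug use are deliberately not followed up, say so.
- Confirm that the battery item and the Alcohol Safety Sheet carry the same level.

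If follow-up is already complete, a sentence stating which level was applied does the same job. The cost is a few words in two places in each document and a check of two forms. No new measure, data source or clinical action is needed.

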## **8.0 SIGNIFICANCE TESTING**

Statistical significance will be considered at  $p < .05$  for each analysis.

## **9.0 SAMPLE SIZE AND POWER (Reference: Protocol p. 21)**

We will recruit a convenience sample of 450 adolescent patients ( $n=450$ ) and expect 300 of them will complete the entire study. With total sample size of 300 youth, there is adequate power (.80) to detect

significant effects ( $p < .05$ ) for adjusted odds ratios of  $\geq 2.0$ , defined as the likelihood that control versus intervention participants initiate or escalate their substance use behaviors from baseline to follow-up, across prevalence levels in the intervention group that range from .20 to .55.

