## C. Preliminary Studies

185 Validation of screening in youth with Chronic Medical Conditions (YCMC) Drs. [name] and [name]  
186 are currently co-principal investigators (PIs) on an NIAAA funded study Validating NIAAA's Brief  
187 Screening Guide in Youth with Chronic Medical Conditions (R01-AA021913). This screening  
188 validation study is exploring alcohol use risk among youth with chronic medical conditions (YCMC)  
189 ages 9-18 years (n=400) receiving care at BCH. Among 403 who have completed baseline  
190 assessments, past year alcohol use was reported by nearly one third (30.8%) of the entire sample,  
191 and over one third (36.5%) of high school youth. Binge drinking was reported by 10.4% of the total  
192 sample, by 12.7% of high school youth, and 37.7% of high school youth who reported past-year  
193 alcohol use. Approximately one sixth of the entire sample (17.2%) and one fifth (20.6%) of high school  
194 youth reported using marijuana in the past year. Sixty percent report being asked in the past year by a  
195 member of their care team about their drinking.

196 Screening rates and practices among physicians. [name] collaborated with the Massachusetts  
197 Department of Public Health on a study to determine alcohol and drug screening rates and practices  
198 among physicians practicing in Massachusetts. A large majority of respondents (86%) reported that  
199 they screen adolescents for substance use annually though only a minority (34%) reported using  
200 appropriately validated tools, leading to the potential for significant under appreciation of substance  
201 use problems and disorders. An outcome of this project was the creation and publication of a  
202 clinical practice guideline for adolescent screening, brief intervention, and referral to treatment  
203 (SBIRT) that was described as "easy to understand and use" during field testing, and ultimately  
204 distributed to every practicing pediatrician and family physician in the state. An updated version of  
205 the guideline was subsequently included in a published policy statement by the American Academy of  
206 Pediatrics.

207 Screening, Brief Intervention, Referral to Treatment (SBIRT) curriculum development. [name] is PI on a  
208 Substance Abuse and Mental Health Services Administration (SAMHSA)-funded medical residency  
209 SBIRT curriculum development project (TI020267). The team designed and adapted SBIRT strategies  

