### **6.2 Analysis of the Primary Outcome Measure (Reference: Protocol p. 20)**

All analyses will be conducted under the principle of intention to treat; all participants will be analyzed as members of the groups to which they were originally randomized to. We will examine the impact of the psychoeducation program on alcohol use, measured from baseline to twelve months, taking into account correlations within individuals, using multivariate mixed-effects models.

Our primary outcome variables will be initiation and escalation of substance use. Initiation of use will be defined as any new use of substances at follow-up among those reporting no past-12-month use at baseline. For alcohol use, escalation will be defined as, among drinkers, any increase in number of drinks (measured by TLFB) from baseline to follow-up. For marijuana use, escalation will be defined as, among users, any increase in days of smoking marijuana (measured by TLFB) from baseline to follow-up.

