#### **Defining Outcomes**

Primary Outcome(s): Past 3-month alcohol use measured by a Brief Frequency variable for alcohol use.

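### The stated 80% power for an odds ratio of 2.0 with 300 completers falls to about 75% at the lower end of its own prevalence range, depends on an unstated denominator, and was not restated for the current primary outcome

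*Supplement*

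**What the plan says.** SAP 9.0, repeated in Protocol section I, plans to recruit 450 and "expect 300 of them will complete the entire study". It continues: "With total sample size of 300 youth, there is adequate power (.80) to detect" adjusted odds ratios of at least 2.0 at p < .05. The odds ratio compares control with intervention on whether "intervention participants initiate or escalate their substance use behaviors from baseline to follow-up", and the claim is made "across prevalence levels in the intervention group that range from .20 to .55". Neither section gives the sidedness, the allocation ratio or the formula. SAP 8.0 adds only that each analysis uses p < .05.

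SAP 6.2 defines the two components on different groups. "Initiation of use will be defined as any new use of substances at follow-up among those reporting no past-12-month use at baseline". Escalation is defined among baseline drinkers for alcohol and among baseline users for marijuana.

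SAP 11.0 then updates section 6.0. The entry of 6/27/2019 gives the primary outcome as "Past 3-month alcohol use measured by a Brief Frequency variable for alcohol use". The entry of 12/16/2020 specifies mixed-effects models of alcohol use from baseline to twelve months. No entry in 11.0 refers to section 9.0.

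**The concern.** There are three questions. Does 300 give 80% power over the whole range claimed? Are there 300 people in the analysis that the claim describes? Does the claim describe the outcome that is now primary?

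Section 9.0 is where a reader judges whether a null result is informative. If its figure is too high, or belongs to another outcome or denominator, a null result could be read as stronger evidence against an effect than the design supports.

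**Working it through.** **Inputs.** From SAP 9.0: 300 completers, odds ratio 2.0 with control having the higher risk, intervention-group prevalence p₁ from .20 to .55, significance level .05. Assumed because not stated: two-sided test, 1:1 allocation (n = 150 per arm). The calculation is unadjusted and so approximates the adjusted logistic model.

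**Formulas.** Control prevalence: p₂ = 2·o/(1 + 2·o), with o = p₁/(1 − p₁). With p̄ = (p₁ + p₂)/2,

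power = Φ{ [ |p₂ − p₁|·√n − 1.96·√(2p̄(1 − p̄)) ] / √(p₁(1 − p₁) + p₂(1 − p₂)) }.

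**Step 1: the plan's own figure at p₁ = .20.** o = .25, so p₂ = .50/1.50 = .333 and p̄ = .2667.
- |p₂ − p₁|·√150 = .1333 × 12.247 = 1.633
- 1.96 × √(2 × .2667 × .7333) = 1.96 × .6254 = 1.226
- √(.1600 + .2222) = .6182
- Power = Φ(.407/.6182) = Φ(.659) = **74.5%**, against a stated 80%.

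**Step 2: across the range, all 300 analysed.**

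| p₁ | p₂ | Power, two-sided | Power, one-sided |
|---|---|---|---|
| .20 | .333 | 74.5% | 83.6% |
| .23 | .374 | 77.8% | 86.1% |
| .25 | .400 | 79.5% | 87.4% |
| .26 | .413 | 80.2% | 87.9% |
| .30 | .462 | 82.5% | 89.5% |
| .40 | .571 | 84.7% | 91.1% |
| .55 | .710 | 82.0% | 89.2% |

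The choice of formula does not explain the gap. At .20, two-sided, unpooled variance gives 75.2%, a Wald test on the log odds ratio 73.5%, exact enumeration of the chi-square test 74.9% and a continuity correction 70.1%. Treating the range as control-group rates makes it worse (57% at .20).

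For 80% at p₁ = .20, the detectable odds ratio is about 2.09, or 172 per arm (344 completers) would be needed. With an odds ratio of 2.1 and 150 per arm, power is 80.5% at .20 and 86.6% at .55.

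**Step 3: the denominator.** If initiation and escalation are one composite per substance, each completer is at risk of one or the other, n stays at 300 and Step 2 applies. If they are tested separately, each test uses a subset.

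Protocol section C gives past-year use in the preliminary study: alcohol 30.8% of the whole sample "and over one third (36.5%) of high school youth"; marijuana 17.2% and 20.6% respectively. Assume that these rates hold in the 300 completers, that past-year use defines drinkers and users, and that each subset splits evenly between arms. Power for an odds ratio of 2.0 over p₁ = .20 to .55 is then:

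| Outcome tested alone | Number analysed | Power |
|---|---|---|
| Alcohol initiation | 300 × .635 to .692 = 191–208 | about 55–70% |
| Alcohol escalation | 300 × .308 to .365 = 92–110 | about 30–43% |
| Marijuana initiation | 300 × .794 to .828 = 238–248 | about 64–77% |
| Marijuana escalation | 300 × .172 to .206 = 52–62 | about 19–27% |

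**Step 4: the current primary outcome.** SAP 9.0 uses an odds ratio for initiating or escalating use. SAP 11.0 now names past-3-month alcohol use on a brief frequency measure, in a mixed-effects model. The documents give no scale, variance or within-person correlation for that measure and no expected rate for that outcome. Its power cannot be derived from them.

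**The case against.** The strongest reply is that the shortfall is small. It is at most 5.5 points, lies between .20 and about .25, and is material only up to about .23. Over the rest of the range the claim holds with some margin. A one-sided 5% test would meet it throughout, and the documents do not state sidedness. All of this stands as a limit on size. It does not remove the point, because the sponsor chose .20 as the lower bound and nowhere declares a one-sided test.

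A reader might go further and infer that the trial has only 19–77% power for its outcomes as defined. The documents do not support that as a flat statement.
- The power statement and the hypotheses use joined wording, initiate or escalate, which is compatible with one composite in all completers.
- The only separate models specified for the intervention effect are by visit, at 6 and 12 months.
- The subset sizes borrow rates from another study. The 30.8% and 17.2% come from a sample aged 9–18, whereas the trial enrolled ages 14–17, later 14–18. With the high-school marijuana rate the lowest figure is about 22% instead of 19%.
- The components appear to have been replaced as primary by the 2019 update. The newer outcome applies to all participants, and a mixed model may use partial follow-up, so these figures say nothing about its power.

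What remains is that no section defines the composite or its analysis set, while SAP 6.2 defines the parts on disjoint groups. The reader cannot tell which power applies.

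**Conclusion.** The concern holds in a limited form. With a two-sided 5% test and equal allocation, the stated 80% is 74.5% at an intervention prevalence of .20 and reaches 80% only from about .26. The claim is therefore wrong at the lower end of its range and right above it. It would be too broad to say that the power is not delivered in general.

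The 300 is valid only for a composite in all completers, which the plan never states. The lower figures in Step 3 depend on separate testing and on the preliminary-study use rates.

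Section 9.0 also no longer matches the primary outcome and model in SAP 11.0. This is a gap within the current plan, not an objection to the change of outcome. A detectable effect in standard-deviation units should not be supplied on the sponsor's behalf, because nothing in the documents supports one for the brief frequency measure.

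**What to change.** Amend SAP 9.0 and Protocol section I; the sample size stays as it is.
1. State the test and allocation, and restate the claim as 80% power, two-sided .05, for an odds ratio of at least 2.1 at intervention prevalences .20 to .55, or for 2.0 at .26 to .55.
2. Say that this applies to a composite of initiation or escalation, per substance, in all completers, and define that composite in SAP 6.2. If the components are to be tested separately, give the expected denominators and the lower power, with the use rates assumed.
3. Label the statement as referring to the initiation/escalation outcome. Add a detectable effect for past-3-month alcohol use under the mixed-effects model, from the sponsor's own rate or variance and correlation assumptions, and state the number expected to contribute data.

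The cost is a wording change in two places, one short calculation by the sponsor, and a stated power that is slightly less favourable. No extra participants are needed.
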